### Statistical Analyses

Using the results of previous web-based intervention studies designed to reduce AD risk in an RCT design [11,56], a 2-point difference in the ANU-ADRI total score between the groups is expected over time [41]. A longitudinal observational study among adults demonstrated that a 1-point increase in ANU-ADRI score is associated with an 8% increase in the risk for developing MCI or dementia, mediated by brain volume, over the following 12 years [57]. A 2.5-point within-group change was found to be statistically significant in a web intervention [11]. Owing to the population health effects that are possible with a scalable remote intervention, these metrics are clinically and statistically meaningful at the individual and group levels.

Exploratory analyses will be performed on an intent-to-treat basis. One-way ANOVA will be used to compare the groups on functional fitness; biomarker measures; health-related variables; and digital, cognitive assessments at baseline. In addition, sex differences in baseline characteristics and change scores will be evaluated using a 2×2 (group and sex) ANOVA. Repeated measures ANOVA will be used to determine the differences over time between the groups. APOE status and the presence of homozygous E4 alleles will be used as a dichotomous variable and as a covariate for change in results after the intervention.

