**Methods:**

The lifestyle intervention consists of a digitally delivered, personalized health coaching program that directly targets the modifiable risk factors for AD. The primary outcome measure is AD risk as determined by the Australian National University-Alzheimer Disease Risk Index; secondary outcome measures are functional fitness, blood biomarkers (inflammation, glucose, cholesterol, and triglycerides), and cognitive function (Repeatable Battery for the Assessment of Neuropsychological Status and Neurotrack Cognitive Battery). Screening commenced in January 2021 and was completed in June 2021.

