**Results:**

Baseline characteristics indicate no difference between the intervention and control groups for AD risk (mean −1.68, SD 7.31; *P*=.90).

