### Participant Recruitment

Participants were recruited in northwest Arkansas using local radio, email, social media advertisements, and word of mouth. The participants who met all the inclusion criteria and none of the exclusion criteria were randomly assigned to one of the groups before any assessments were completed.

The goal sample size for this study is approximately 200 participants. This sample size is considered sufficient to achieve random assortment, which was validated after examining the baseline characteristics of both groups. Cross-sectional, between-group differences in the baseline ANU-ADRI scores will be assessed using analysis of variance (ANOVA). Longitudinal studies following cognitively intact older adults have documented a 0.8 RBANS standard score change (SD 13.8) over a 12-month period [54]. Owing to the younger and wider age range to be recruited, we conservatively estimated a 1.75 standard score change with a comparable SD 10 among the control participants. In a 12-month pilot study of a similar intervention, a 5.8 (SD 7.4) standard score point increase on RBANS (ie, improvement) was found [55]. Assuming no additional improvement owing to a longer intervention, a sample size of 100 participants per group provides 80% power to detect a difference of 3.3 points between the intervention groups on the RBANS total index score (Cohen *d*=0.33) with an α of .05 and accounting for up to 20% attrition.

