### Conclusions

The results of this study can produce a novel and highly scalable intervention strategy to reduce the risk of cognitive decline before MCI or AD diagnoses occur. The primary outcome in the DCMARVel trial is AD risk reduction as determined by ANU-ADRI [11]. With the wide range of secondary outcomes (eg, physical, blood biomarkers, and psychosocial), the relative contribution to AD risk reduction can be estimated in addition to changes over time. As the HC program is designed to address multiple factors contributing to vascular disease (eg, physical activity and dietary habits), the intervention is expected to improve cognitive outcomes over time by significantly reducing AD risk using a digital and scalable format.

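### The expected 2-point ANU-ADRI difference is called statistically meaningful without support: the only power figure is for RBANS, a secondary outcome, and adequate power for the primary outcome is neither shown nor ruled out

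*Protocol article*

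**What the plan says.** All references are to the protocol article.

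- **Primary outcome.** Abstract, Methods: "The primary outcome measure is AD risk as determined by the Australian National University-Alzheimer Disease Risk Index". Discussion, Conclusions: "The primary outcome in the DCMARVel trial is AD risk reduction as determined by ANU-ADRI".
- **RBANS.** The Abstract lists it among the secondary outcomes, under "cognitive function (Repeatable Battery for the Assessment of Neuropsychological Status and Neurotrack Cognitive Battery".
- **Sample size.** Participant Recruitment: "The goal sample size for this study is approximately 200 participants". The justification is that 100 per group "provides 80% power to detect a difference of 3.3 points between the intervention groups on the RBANS total index score", with Cohen d 0.33, alpha .05 and up to 20% attrition.
- **ANU-ADRI effect.** Statistical Analyses: "a 2-point difference in the ANU-ADRI total score between the groups is expected over time". The paragraph adds a risk increase of 8% per point from an observational study and a significant 2.5-point within-group change in a web intervention. It concludes that "these metrics are clinically and statistically meaningful at the individual and group levels". ANU-ADRI Tool separately gives 2 points as the clinically meaningful change.
- **Observed spread.** Abstract, Results: "mean −1.68, SD 7.31". Table 2 gives 7.34 and 7.32 by arm, with 101 and 103 participants.
- **Analysis.** Repeated measures ANOVA for differences between groups over time, with visits at baseline and 4, 12 and 24 months.

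**The concern.** A significant change within one group of another study does not show that a smaller difference between two groups would be significant here. Whether it would depends on this trial's SD, its numbers, and how strongly baseline predicts follow-up. The paragraph that makes the claim gives none of these for the 2-point difference.

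The 80% in the article belongs to a different endpoint. A reader looking for assurance on the primary question finds only that figure and the word "meaningful". If the correlation over two years is moderate and the contrast is at 24 months, a real 2-point benefit has roughly even odds of missing significance and could be reported as no effect. The choice of contrast also matters, because a baseline-adjusted comparison and a change-type comparison of the same data differ in power.

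**Working it through.** **Inputs.** Difference 2 points (Statistical Analyses); SD 7.31 (Abstract, Table 2); 100 per group less 20% = 80 per arm (Participant Recruitment); 101 and 103 if nobody is lost (Table 2). Assumed: two-sided alpha .05, and a follow-up SD equal to the baseline SD. The correlation r between visits is not given, so a range is shown. Power is from the noncentral t distribution.

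**1. The article's own power figure (RBANS).** Difference 3.3, SD 10, so d = 0.33. In an unadjusted two-sample comparison:
- 100 per arm: SE = 10 × √(2/100) = 1.414, 3.3/1.414 = 2.33, power about 64%.
- 80 per arm: SE = 10 × √(2/80) = 1.581, 3.3/1.581 = 2.09, power about 55%.

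The stated 80% is not reproduced from these inputs. It can be reached with inputs not stated for this calculation, for example baseline adjustment with r about 0.67 at 80 per arm.

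**2. ANU-ADRI, unadjusted at 24 months.** d = 2/7.31 = 0.274.

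| | 80 per arm | 101 and 103 |
|---|---|---|
| SE = 7.31 × √(1/n₁ + 1/n₂) | 1.156 | 1.024 |
| t for an observed 2 points | 1.73 | 1.95 |
| P | .086 | .052 |
| Power for a true 2 points | 41% | 49% |
| Difference detectable with 80% power | 3.26 | 2.88 |

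**3. ANU-ADRI, using baseline, 80 per arm.**
- ANCOVA at 24 months: SD = 7.31 × √(1 − r²).
- Change score at 24 months: SD = 7.31 × √(2(1 − r)).
- Mean of the three follow-ups, baseline-adjusted, with a 2-point effect at each visit and equal correlations between all visits: SD = 7.31 × √((1 + 2r)/3 − r²).

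| r | ANCOVA SD | ANCOVA power | Change-score SD | Change-score power | Averaged SD | Averaged power |
|---|---|---|---|---|---|---|
| 0.5 | 6.33 | 51% | 7.31 | 41% | 4.72 | 76% |
| 0.6 | 5.85 | 58% | 6.54 | 49% | 4.47 | 80% |
| 0.7 | 5.22 | 67% | 5.66 | 60% | 4.07 | 87% |
| 0.8 | 4.39 | 82% | 4.62 | 78% | 3.48 | 95% |

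ANCOVA at 24 months reaches 80% power at r of about 0.79 with 80 per arm, or about 0.72 with all 204 retained.

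**4. An observed 2-point difference under ANCOVA at r = 0.5.** With 80 per arm, SE = 6.33 × √(2/80) = 1.001, t = 2.00, P = .047. With all 204, P = .025.

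**The case against.** The strongest reply is that nobody plans an unadjusted test at 24 months. The plan is repeated measures ANOVA over four visits, which uses baseline and the intermediate data. A reader might infer from P = .086 and P = .052 that a 2-point difference would fail to reach significance in this trial. The article does not support that: with baseline adjustment and r = 0.5 the same difference is significant, and a constant effect averaged over three visits would give 76% to 95% power. ANU-ADRI also contains items that hardly change, such as education and history of head injury, so a high correlation is credible, though undocumented. This part of the reply stands, and those P values describe only an unadjusted single-visit test.

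Second, sizing a trial on a secondary outcome is not an error in itself, the 80% is plainly labelled as RBANS, and no power is claimed for ANU-ADRI. A condensed article may leave a primary-outcome calculation to the full protocol. That also stands, so the missing calculation alone is not the point.

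Third, the disputed sentence covers several metrics and appeals to population health effects. It is loosely worded, but the 2-point between-group difference is among those metrics and statistical meaning is claimed at group level. That claim is in the article and can be tested against the article's own SD. It does not follow from what is offered in its support.

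**Conclusion.** The point holds in a limited form. The claim that a 2-point between-group difference is statistically meaningful has no support in the article, and the only power figure concerns another endpoint. For a contrast at 24 months with 80 per arm, power is 41% unadjusted, 51% to 82% with baseline adjustment and 41% to 78% with change scores, for r from 0.5 to 0.8. Averaging a constant effect over three visits raises it to 76% to 95%.

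A reader might go further and conclude that the trial is underpowered for its primary outcome. That is plausible for a 24-month contrast with moderate correlation, but it is not shown, because the article fixes neither the correlation nor the time course. Adequate power is unsupported, not disproved. The figures assume a two-sided test and a follow-up SD equal to the baseline SD of 7.31. Severity is should-fix.

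**What to change.** 1. Name a baseline-adjusted (ANCOVA-type) comparison of ANU-ADRI as the primary analysis, and fix the visit or average of visits it targets before outcome data are examined. It uses data already being collected. At 24 months and r = 0.5 it gives 51% power against 41% for the change score.
2. Replace the claim of statistical meaningfulness with the power for 2 points and the detectable difference, at SD 7.31 and 80 per arm, over a stated range of correlations.
3. State that the result will be interpreted from the confidence interval against the 2-point threshold, and that a non-significant result will not be read as excluding a 2-point benefit.
4. Label the RBANS calculation as secondary. Do not carry its 80% forward unchecked: either state the inputs that produce it or correct it.

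The cost is rewording two paragraphs, one analysis specification, and a less favourable statement about the primary outcome. Relabelling the RBANS calculation alone would not be enough. No extra participants are needed.

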## Methods

### Study Design and Participants

This is a single-site, 2-year randomized controlled trial (RCT). The participants include men and women aged from 45 to 75 years who have risk factors for dementia. Each participant has been informed of the purpose of the intervention and has agreed to be assigned randomly into 1 of the 2 study groups (HC or HE).

To be included in the study, the participants must have at least 2 positive risk factors for AD as determined by the Australian National University-Alzheimer Disease Risk Index (ANU-ADRI) [11] and not more than 1 protective factor (eg, high level of physical activity). Textbox 1 shows the complete list of the inclusion and exclusion criteria. The participants will complete 4 study visits over 2 years: at baseline and 4, 12, and 24 months.

Inclusion and exclusion criteria.

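### Repeated measures ANOVA, in its standard form, would leave out participants with a missed visit and so works against the stated intent-to-treat basis; a mixed model using all observed visits should replace it

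*Protocol article*

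**What the plan says.** The protocol article (Statistical Analyses) describes the analysis population in one sentence: "Exploratory analyses will be performed on an intent-to-treat basis". No other sentence says who is analysed.

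The same paragraph gives the longitudinal method: "Repeated measures ANOVA will be used to determine the differences over time between the groups". The other analyses in that paragraph are baseline comparisons, a group-by-sex ANOVA aimed at sex differences, and the use of APOE status as a covariate. Repeated measures ANOVA is therefore the only method named for the comparison of arms over time, and the primary outcome, the ANU-ADRI total score, falls to it by default.

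Study Design and Participants sets the schedule: "The participants will complete 4 study visits over 2 years: at baseline and 4, 12, and 24 months". Participant Recruitment sizes the trial "accounting for up to 20% attrition". The article mentions no imputation and no mixed model.

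**The concern.** Classical repeated measures ANOVA works on complete rows. A participant who attends baseline, month 4 and month 12 but misses month 24 is removed entirely, including the visits that were observed. If the plan is followed as written, without imputation, any attrition turns the analysis into one of completers. That is not what intent-to-treat usually means. The attrition allowance does not help, because it enters the sample size and does not keep dropouts in the analysis.

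Two things are at stake. One is information: data already collected are discarded. The other is possible bias. The arms differ in contact, with weekly or twice-weekly messages and monthly meetings under coaching against biweekly emails in control. The reasons for leaving could therefore differ. If coached participants who are not improving tend to leave, those who remain look better than the arm as randomised.

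**Working it through.** **The plan's own figure.** The attrition allowance is part of the power statement: "a sample size of 100 participants per group provides 80% power to detect a difference of 3.3 points between the intervention groups", on RBANS, with control SD 10, hence *d* = 0.33. Two-sided power at α = .05 is approximately Φ(*d*·√(n/2) − 1.96).
- n = 100 per group: Φ(0.33 × 7.071 − 1.96) = Φ(0.373) = 64.6%.
- n = 80 per group (after 20% loss): Φ(0.33 × 6.325 − 1.96) = Φ(0.127) = 55.1%.

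The stated 80% is not reproduced. That is a separate matter, and nothing below depends on it.

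**Participants excluded.** Inputs: 204 participants with baseline data (101 education, 103 coaching; Table 2) and the 20% ceiling.
- Complete cases: 204 × 0.80 = 163. Excluded: 204 − 163 = 41.
- If a share q of those who finish also misses each of the 4- and 12-month visits (an assumption; no rate is given), complete cases = 204 × 0.80 × (1 − q)².

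| q | Complete cases of 204 |
|---|---|
| 0 | 163 |
| 2% | 157 |
| 5% | 147 |
| 10% | 132 |

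**Bias with no true effect.** From the article: ANU-ADRI SD 7.31, 101 and 103 per arm, 20% dropout. Assumed: equal correlation ρ between visits, dropout after month 4 in both arms, and dropout depending on the observed 4-month change in the coaching arm only, with slope 0.1, 0.2 or 0.3 per point. There were 1,500 simulated trials per scenario. The completer difference in 24-month change (coaching minus education; negative favours coaching) was:

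| ρ | slope 0.1 | slope 0.2 | slope 0.3 |
|---|---|---|---|
| 0.6 | −0.36 | −0.64 | −0.87 |
| 0.7 | −0.35 | −0.54 | −0.64 |
| 0.8 | −0.22 | −0.37 | −0.52 |

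A likelihood estimate from all observed visits lay between −0.04 and +0.05.

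To put these on the scale of sampling error, the SE of the completer difference is 7.31 × √(2(1 − ρ)) × √(1/81 + 1/82).
- ρ = 0.6: SE = 6.54 × 0.157 = 1.02, so the largest bias is 0.87/1.02 = 0.85 SE.
- ρ = 0.8: SE = 4.62 × 0.157 = 0.72, so the smallest bias is 0.22/0.72 = 0.30 SE.

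A nominal two-sided 5% test would then reject in about 6% to 14% of trials.

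**Bias with a true effect of −2.0.** A separate simulation used 200,000 per arm and ρ of 0.5, 0.7 and 0.8. Assumed true differences at the four visits were 0, −1, −1.5 and −2. Dropout was 20% after month 4, with a log-odds slope of 1 (moderate) or 2 (strong) per SD of 4-month change. The estimated 24-month difference was:

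| Dropout mechanism | Completers | Model valid under missing at random |
|---|---|---|
| Completely random | −1.99 to −2.01 | −1.99 to −2.01 |
| Outcome-related, same in both arms | −1.97 to −2.00 | −1.95 to −2.00 |
| Outcome-related, coaching arm only, moderate | −2.29 to −2.60 | −1.96 to −2.01 |
| Outcome-related, coaching arm only, strong | −2.49 to −2.93 | −1.99 to −2.01 |

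The two simulations agree: about 0.2 to 0.9 points in favour of coaching under one-arm outcome-related dropout, and about zero otherwise. The good result for the likelihood-type model is partly built in, because dropout was made to depend only on observed data.

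**The case against.** The strongest reply is that the article nowhere says incomplete participants will be removed. An analysis plan that is not shown could add imputation, or could use the ANOVA label for a mixed model; either would reconcile the two sentences. Handling of missing visits is also something an article commonly leaves to that plan. This stands in part. Silence on imputation is not the point. The point is that the article does name a method, and its usual form pulls against the principle stated beside it. An unseen plan would have to supplement or replace that method.

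Several stronger readings are tempting and are not supported:
- A reader might infer that 20% dropout is expected, or that at least 20% will be discarded. The article gives 20% as an upper planning allowance.
- A reader might infer that intent-to-treat is promised for every analysis. The sentence literally covers exploratory analyses. It is the only such statement and it opens the paragraph that names the method, but its reach to the primary outcome is unclear.
- A reader might infer that the treatment effect will be biased. No passage shows that dropout will relate to outcome differently by arm, and unequal dropout rates alone would not produce this bias.
- A reader might add that unequally spaced visits break sphericity. Unequal spacing is not in itself a violation, standard corrections exist, and the simulations assumed equal correlations, under which sphericity holds.

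**Conclusion.** The point holds in a limited form, and the wording should be fixed. Applied in its standard form without imputation, the named method gives a completer analysis that sits badly with an intent-to-treat basis. At the attrition ceiling it would leave out about 41 of 204 participants, more if isolated visits are missed and fewer if attrition stays below the ceiling. That count rests only on the article's figures and the method's usual behaviour.

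The bias is a conditional risk. The 0.2 to 0.9 points, about 10% to 45% of the 2-point target, rest on assumed visit correlations, dropout timing and strength, and on outcome-related dropout in the coaching arm alone. The documents do not support reading it as a forecast, or as evidence that the planned analysis must manufacture a benefit.

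**What to change.** In Statistical Analyses, replace repeated measures ANOVA with a likelihood-based mixed model for repeated measures: visit as a categorical factor, group-by-visit interaction, unstructured covariance, and either the baseline score as a covariate or baseline means constrained equal. Include all randomised participants with all observed visits. State that the intent-to-treat basis applies to the primary ANU-ADRI analysis and not only to exploratory ones.

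The cost is a change of analysis wording; the data, visits, sample size and software needs are unchanged. The downside is reliance on missing at random, so add a sensitivity analysis under missing not at random. The change is best made before outcome data are analysed.

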### Purpose

Of the studies on multi-domain lifestyle interventions for reducing AD risk, few have tested middle-aged individuals and few have implemented digital interventions. Using the intervention program earlier in the disease course can maximize its benefits, and using digital technologies rather than relying on face-to-face implementation can greatly increase the reach and scalability of these programs. Therefore, the purpose of the DCMARVel trial is to determine the effects of a 2-year digital, multi-domain lifestyle intervention on AD risk among at-risk middle-aged to older adults (45-75 years). Moreover, the digital and personalized nature of the intervention provides the opportunity to explore the variables that may contribute to the accessibility and subsequent adherence to an AD risk reduction intervention. This paper outlines the study protocol and baseline characteristics of the study population. The main aims of this study are as follows: (1) to determine the effect of a 2-year digital, multi-domain AD risk reduction intervention on the overall risk of AD in adults at risk of developing the disease; (2) to determine the effect of digital interventions on the rate of cognitive decline; and (3) to determine the effect of digital interventions on the changes in general health outcomes.

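### The repeated measures ANOVA named for follow-up is not tied to the 2-year effect: as a group-by-time test it can be significant with no effect at 24 months, and it can have less power than a baseline-adjusted 24-month contrast

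*Protocol article*

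**What the plan says.** - **Aim.** Under Purpose, aim 1 is "to determine the effect of a 2-year digital, multi-domain AD risk reduction intervention on the overall risk of AD".
- **Primary outcome.** The Conclusions state that "The primary outcome in the DCMARVel trial is AD risk reduction as determined by ANU-ADRI".
- **Visits.** Study Design and Participants: "The participants will complete 4 study visits over 2 years: at baseline and 4, 12, and 24 months". Table 1 has the ANU-ADRI components collected at all four.
- **Test.** Statistical Analyses: "Repeated measures ANOVA will be used to determine the differences over time between the groups". No model term, contrast or visit is singled out. The paragraph opens by describing its analyses as exploratory and by intention to treat.
- **Expected effect.** The same section says that "a 2-point difference in the ANU-ADRI total score between the groups is expected over time", again without naming a visit.
- **Other analyses of change.** APOE status is a covariate for change in results, and "sex differences in baseline characteristics and change scores will be evaluated using a 2×2 (group and sex) ANOVA". Neither is put forward as the test of the intervention on ANU-ADRI.

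**The concern.** Aim 1 concerns what two years of the intervention do to AD risk. A group-by-time test over four visits asks whether the difference between the arms varies anywhere among 0, 4, 12 and 24 months. A gain seen at 4 months and gone by 24 months is enough to make it significant. The same test spreads its sensitivity over three degrees of freedom, so for some effect profiles it is weaker at finding a 24-month difference than one contrast aimed at it. If the sentence is followed as it stands, a significant result need not mean a 2-year benefit, and a real 2-year benefit may be missed more often than necessary.

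**Working it through.** **The plan's own figure.** The article gives no power for this test or for ANU-ADRI. Its only power statement (Participant Recruitment) concerns a two-group difference in RBANS, so there is no figure to reproduce here.

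**Inputs**
- SD of ANU-ADRI total 7.31 (Abstract, Results; Table 2), taken as the SD at every visit; variance 7.31² = 53.44.
- Effect size 2 points (Statistical Analyses).
- n = 80 analysed per arm: 100 per arm less 20% attrition (Participant Recruitment).
- α = 0.05, taken as two-sided.
- Correlation ρ between visits: not in the document. Assumed equal for all pairs of visits and varied from 0.5 to 0.9.

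**Formulas.** Let d_t be the true difference between arms at visit t.
- Group-by-time test: noncentral F with 3 and 3(2n − 2) = 474 df, noncentrality λ = (n/2) · Σ(d_t − mean d)² / [SD²(1 − ρ)].
- 24-month change score: SE² = (2/n) · 2(1 − ρ) · SD².
- 24-month contrast adjusted for baseline: SE² = (2/n) · (1 − ρ²) · SD².

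**Step 1: no effect at 24 months.** For 2 points at 4 months only, d = (0, 2, 0, 0), mean 0.5, sum of squares 3 × 0.25 + 2.25 = 3. At ρ = 0.7, λ = 40 × 3 / (53.44 × 0.3) = 7.49, so the test rejects in 61.8% of trials. Percentage of trials significant:

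| Effect at 0, 4, 12, 24 months | ρ = 0.5 | ρ = 0.7 | ρ = 0.8 | 24-month test |
|---|---|---|---|---|
| 0, 2, 0, 0 | 39.6 | 61.8 | 80.9 | 5 |
| 0, 2, 1, 0 | 36.5 | 57.6 | 77.1 | 5 |
| 0, 2, 2, 0 | 51.4 | 75.6 | 91.4 | 5 |

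**Step 2: a real 2-point effect at 24 months.** Linear growth gives d = (0, 0.33, 1, 2), mean 0.83, sum of squares 2.33. At ρ = 0.7, λ = 40 × 2.33 / 16.03 = 5.82 and power is 50.1%. The adjusted contrast has SE = √(0.025 × 0.51 × 53.44) = 0.825, ratio 2/0.825 = 2.42 and power 67.3%. A sustained effect (0, 2, 2, 2) has sum of squares 3, hence λ = 7.49 and power 61.8%. Power in %, group-by-time / 24-month change score / 24-month baseline-adjusted:

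| ρ | Linear growth | Sustained effect |
|---|---|---|
| 0.5 | 31.4 / 40.5 / 51.0 | 39.6 / 40.5 / 51.0 |
| 0.7 | 50.1 / 60.3 / 67.3 | 61.8 / 60.3 / 67.3 |
| 0.8 | 69.3 / 77.6 / 81.8 | 80.9 / 77.6 / 81.8 |
| 0.9 | 95.2 / 97.0 / 97.6 | 98.6 / 97.0 / 97.6 |

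An effect at 24 months only, or one rising linearly to 2 points at 12 months and then flat, also has sum of squares 3 and gives the sustained column.

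**Step 3: check.** A simulation of 3,000 trials at ρ = 0.7 gave 62.8% for the 4-month-only effect (formula 61.8), 49.5% for linear growth (50.1) and 62.8% for the sustained effect (61.8).

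**The case against.** **The text is brief and calls these analyses exploratory.** The article names no term, contrast or success rule, the group-by-time term is inferred, and a fuller plan may name a 24-month contrast. This stands as a limit on the wording. It does not dispose of the point: the article does state a method for between-group differences over follow-up, gives no other for its primary outcome, and does not link that method to the question in aim 1.

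**A trajectory test fits the article's language.** The expected difference is described only as arising over time, aim 2 concerns a rate of decline, and two years is the length of the intervention; no sentence makes 24 months the sole endpoint. This is fair, and it is why the group-by-time test should be kept as supportive. It does not make a test that an early, vanished difference can trigger an answer to the 2-year question.

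**The fading effect is a stress case.** Coaching runs for the whole study and nothing in the article predicts decay. That is correct; Step 1 shows what a significant result could mean, not what is likely to happen.

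**The power loss is not general.** This stands. The sample size paragraph assumes no further RBANS gain from a longer intervention. If ANU-ADRI also levelled off by 12 months, the sustained column would apply: the group-by-time test is then about level with a raw change score or up to 3 points better, and its deficit against the adjusted contrast is 11 points at ρ = 0.5, between 5 and 6 at 0.7, about 1 at 0.8, and reversed at 0.9.

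**Two stronger readings that the document does not support.** A reader might infer that the group main effect averaged over all four visits, baseline included, is the intended test. Its power would be only about 27 to 37% for a sustained effect, but the wording points to the interaction. A reader might also infer that baseline is handled as an outcome or through raw change scores in the primary comparison. The article does not say how baseline enters, and its change-score sentence concerns sex differences only.

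**Conclusion.** The point holds in a limited form. The one general follow-up test that the article names is not tied to the 2-year effect. On its natural reading it can be significant with no effect at 24 months: about 40 to 81% of trials for a 2-point effect at 4 months only, at ρ from 0.5 to 0.8, against 5% for a 24-month test. This part needs only that the group-by-time term is meant.

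The power part is conditional. Against a baseline-adjusted 24-month contrast the loss is 17 to 20 points for linear growth at ρ of 0.5 to 0.7, about 13 points at 0.8 and 2 at 0.9. For a sustained effect it is about 11 points at 0.5 and 5 to 6 at 0.7, and it closes by 0.8 to 0.9. It would be wrong to conclude that the named test always costs power.

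All figures rest on SD 7.31 at every visit, 80 analysed per arm, equal correlation between visits, and a correlation that is assumed because the document gives none.

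**What to change.** Before any 24-month data are seen, state one primary test: the between-group difference in ANU-ADRI total at 24 months, adjusted for baseline ANU-ADRI, taken as a 1-df contrast from the longitudinal model. Keep the group-by-time test and the 4- and 12-month contrasts as supportive. Say whether this analysis lies outside the paragraph labelled exploratory. Adjustment for age and sex is optional.

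The cost is a change of wording: no extra visits, measurements or participants. The one downside is that an effect confined to the early visits becomes a supportive result rather than the primary one.
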